### Specific objectives

Implement, in five randomly selected districts, a composite structural intervention: to build skills and support young women to apply to available government support programs; to make support programs more accessible to young women; and to create an enabling environment for young women to exercise protective choices.Measure the impact of the intervention on HIV rates in marginalized young women aged 15–29 years living in intervention districts, compared with young women living in five randomly selected control districts.Measure the impact of the intervention on intermediate outcomes in a behaviour change model in young women and young men, comparing intervention and control districts.Document costs of the intervention package in relation to its outcomes, to calculate costs per case averted and confront the cost implications of its wider roll-out.

A broader outcome, if the trial indicates impact on HIV rates, will be to stimulate further trials of structural interventions appropriate to the context with HIV infections as an endpoint. This will be relevant in Southern Africa and in other regions. In the meantime, the findings from Botswana should make a case for scaling up the interventions in that country.

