### Outcomes

The *primary outcome* is HIV prevalence in young women aged 15–29 years, measured in an impact survey in the five intervention and five control (second wave of intervention) districts. We will undertake rapid HIV screening testing, using Alere Determine units to test finger prick blood samples for HIV1 and HIV2 antibodies. We will not perform confirmatory testing for those that test reactive on this screening test. However, those reactive on the screening test will be referred to their local government clinic for confirmatory testing, counselling, and treatment if appropriate.

*Secondary outcomes* will rely on responses to a questionnaire for men and women aged 15–29 years administered in the impact survey in intervention and control districts. We will measure intermediate outcomes between knowledge and behaviour, according to the CASCADA behaviour change model [55, 56], based on the Theory of Planned Behaviour [57]. CASCADA is an acronym for a partial order of intermediates between knowledge and action: Conscious knowledge, Attitudes, Subjective norms, intention to Change, Agency to make the change, Discussion with family, peers and neighbours, and finally Action. The model does not assume that intermediate steps between conscious knowledge and action are necessarily linearly related. We have used the CASCADA model in resource-poor settings to support analysis and interpretation in cross-sectional studies examining health-related behaviours [58, 59], to guide design of interventions [50, 60, 61] and as a framework for qualitative and quantitative analysis of intervention effects [62, 63]. In this trial, the questionnaire will collect information on the CASCADA sequence of intermediate variables for use of government programs, engagement in transactional sex, gender violence, physical intimate partner violence, multiple partners, and condom use.

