We will use multiple-imputation to deal with missing data [72]. All statistical tests will be two-sided at the 0.05 level of significance. The Bonferroni method will adjust the level of significance for testing for secondary outcomes to keep the overall level at alpha = 0.05. We will express results as effect or odds ratio/relative risk reduction for binary outcomes, standard errors, corresponding two-sided 95% confidence intervals and associated *p*-values.

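### Secondary outcomes: Holm's step-down procedure would meet the plan's own 0.05 familywise target and reject at least as much as plain Bonferroni (an optional gain; Bonferroni is valid)

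*Protocol article*

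**What the plan says.** The multiplicity rule is one sentence in Statistical methods: "The Bonferroni method will adjust the level of significance for testing for secondary outcomes", with the stated purpose of holding the overall level at 0.05. The same paragraph states: "All statistical tests will be two-sided at the 0.05 level of significance". It promises effect estimates and standard errors with "corresponding two-sided 95% confidence intervals and associated" p-values. It does not say that the intervals for secondary outcomes are widened to match the Bonferroni threshold.

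The secondary family is described under Outcomes. The survey covers a behaviour-change sequence "for use of government programs, engagement in transactional sex, gender violence, physical intimate partner violence, multiple partners, and condom use". That makes six topics, asked of women and men, each with up to seven CASCADA steps. The number of tests is not given. The third item under Specific objectives is to "Measure the impact of the intervention on intermediate outcomes in a behaviour change model in young women and young men", so these comparisons are a stated aim of the trial.

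The primary outcome "is HIV prevalence in young women aged 15–29 years, measured in an impact survey" is tested by a district-level two-sample t-test and lies outside the Bonferroni family. For the secondary comparisons the article says only that clustering will be allowed for.

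**The concern.** The only stated purpose of the correction is a familywise level of 0.05. Holm serves that purpose under the same conditions, with no assumption about how the outcomes are correlated, and never rejects less. Its extra rejections come mostly when several outcomes shift at once, as could happen if the intervention works along the behaviour-change sequence. If few districts also mean few degrees of freedom, each division of alpha costs a lot of power. Some real effects on intermediate outcomes could then miss significance when an equally strict familywise procedure would have detected them.

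**Working it through.** **1. The plan's own figure.** With m tests each at 0.05/m, the familywise error is at most m × 0.05/m = 0.05. Under independence it is 1 − (1 − 0.05/m)^m: 0.0490 for m = 6, 0.0489 for m = 12 and 0.0488 for m = 42. Bonferroni delivers the stated level.

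**2. Why Holm never rejects less.** Order the p-values p(1) ≤ … ≤ p(m). Holm rejects p(1), p(2), … in turn while p(j) ≤ 0.05/(m − j + 1), and stops at the first failure. Each threshold is at least 0.05/m. If Bonferroni rejects r hypotheses, the r smallest p-values are all ≤ 0.05/m, so they pass Holm's first r steps. The first threshold is identical, so the methods can differ only after a first Bonferroni rejection. For m = 12 the thresholds run 0.05/12 = 0.0042, 0.05/11 = 0.0045, up to 0.05.

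**3. Inputs for the size of the gain.**
- From the article: two-sided 0.05; five districts per arm; six topics, two sexes, seven CASCADA steps.
- Assumed: m = 12 (6 × 2) or 42 (6 × 7); every secondary test a t-test on district means with 5 + 5 − 2 = 8 df; equal correlation of 0.3 or 0.6 between outcomes; a common size for all true effects.
- Smaller effect: noncentrality 3.15. This matches the primary design in Sample size: variance = 0.23 × 0.77/650 + 0.1725 × 0.8275/650 + 0.119² × (0.23² + 0.1725²) = 0.00166; SE = √(0.00166/5) = 0.0182; 0.0575/0.0182 ≈ 3.15. Unadjusted power on 8 df is 79%.
- Larger effect: noncentrality 5, unadjusted power 99%. It is included because Sample size says that power for secondary outcomes is greater than for the primary, without a figure.

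**4. Bonferroni power from the noncentral t.** For m = 12 the critical |t| on 8 df is 3.96, against 2.31 unadjusted. Power is 31% (smaller effect) and 80% (larger). For m = 42 the critical value is 4.90 and power is 15% and 57%.

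**5. Holm by simulation** (20,000 trials per setting; ranges cover correlation 0.3 and 0.6). Power per true effect, Bonferroni v Holm:

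| m | Effect | One-sixth real | Half real | All real |
|---|---|---|---|---|
| 12 | smaller | 31% v 31–32% | 31% v 34–35% | 31% v 42–44% |
| 12 | larger | 80% v 81% | 80% v 85–86% | 80% v 94–97% |
| 42 | smaller | 15% v 16% | 15% v 16–17% | 15% v 18–21% |
| 42 | larger | 57% v 59% | 57% v 64% | 57% v 79–83% |

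The gains are therefore about 0–2 points, 1–7 points and 3–26 points. Independent runs agree to about one point. No simulated trial had a Bonferroni rejection that Holm missed.

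**6. Sensitivity to the 8 df.** With normal test statistics, correlation 0 to 0.3, and effects sized for 80% unadjusted power, the gains for m = 6 to 42 are 0–1 point (one-sixth real), 2–3 points (half) and 5–12 points (all).

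**7. What Holm gives up.** With m = 12 and half the effects real, realised familywise error goes from about 2.2–2.4% to 3.0–3.1% (smaller effect) and from about 2.2–2.5% to 3.8–4.2% (larger). The highest Holm value in any mix with some true nulls was about 4.5%. Bonferroni's expected number of false positives is (true nulls) × 0.05/m, for example 6 × 0.05/12 = 0.025, and never exceeds 0.05. Holm's in the same larger-effect setting was 0.042–0.049, and Holm has no such general bound.

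**The case against.** The strongest reply is that nothing here is wrong. Bonferroni is prespecified, standard, and meets the target the article sets; no section promises a more powerful method. That stands, and it is why this is a suggestion for efficiency.

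Four stronger readings are tempting, and the article supports none of them:
- *Real effects will be reported as absent.* A result above an adjusted threshold is not a declaration of no effect, and the article commits to estimates and intervals that would show it.
- *Bonferroni buys no error control at all.* The familywise bound is the same, but Bonferroni's realised error is lower when some nulls are true, and it also bounds the expected number of false positives. The accurate statement is that it buys nothing against the stated familywise target.
- *The secondary tests have 8 df.* The district-level t-test is fixed only for the primary outcome. For the secondary tests, 8 df is an assumption.
- *The CASCADA chain makes all outcomes move together.* Outcomes says the model does not require the steps to be linearly related. The all-real rows are the optimistic end, and with few real effects the gain is close to nil.

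It can also be said that Bonferroni has simple matching intervals and Holm does not. That is true in general. But the article specifies 95% intervals, not intervals at level 1 − 0.05/m, so as written it does not take up that advantage. An interval that excludes the null beside a test that misses its adjusted threshold can already occur under the current text.

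**Conclusion.** The point holds as an optional improvement of low severity. Holm meets the article's stated goal under any dependence and rejects everything Bonferroni rejects. The power gain runs from almost nothing when few effects are real to roughly 3–26 points per true effect when all are, given 12 to 42 tests, 8 df, correlation 0.3–0.6 and the two assumed effect sizes. None of these inputs is fixed by the article for the secondary outcomes, so the range shows what is possible and does not forecast this trial. The validity of the analysis, the primary test and the sample size are not in question.

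**What to change.** In Statistical methods, replace the Bonferroni sentence with:

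> Secondary outcomes will be tested with the Holm step-down procedure at a familywise level of 0.05; Holm-adjusted p-values will be reported beside 95% confidence intervals labelled as unadjusted for multiplicity.

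The cost is one sentence, to be settled before group labels are unmasked. The planned software is an interface to R, where Holm is a standard p-value adjustment, and no extra data are needed. The sponsor would accept a realised familywise error nearer to 0.05 and the loss of the bound on expected false positives. If that bound or simultaneous intervals matter more, keeping Bonferroni is defensible; the article should then say so and report intervals at level 1 − 0.05/m.

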### Ethics

The trial received ethical approval from the Health Research and Development Committee (HRDC) in the Ministry of Health, Botswana, on 8 August 2013, HRDC protocol number 00724.

#### Informed consent

The research team will seek the agreement of the district leadership in districts randomized to receive the intervention, including the district commissioner, the head of the district health management team and the district AIDS coordinator. We will also seek agreement to participate from the leadership (the chairman of the village development committee and the village chief) in all communities in the intervention districts. In the process of cluster randomization of whole districts to the intervention package it will not be logistically feasible to obtain informed consent from all those individuals in the districts who might be exposed to interventions. The trial is about the impact of the *offer* of the intervention package: the decision to participate or not in any element of the package rests with the individual residents of the intervention districts.

For the impact survey, interviewers will seek informed consent from all respondents. They will explain the nature and purpose of the survey and its voluntary character. They will explain that participants may decline to answer any questions and may terminate the interview at any time. They will ask respondents for their consent to participate, including giving a finger prick blood sample for rapid screening HIV testing, and participants will sign to indicate their consent. For participants under age 16, a parent or guardian of the young person will sign to indicate their consent. The young person will also be asked to assent to participate.

#### Confidentiality

Training of fieldworkers will emphasise their responsibility for maintaining confidentiality of all information they have access to during the work. We will report only grouped findings, in a way that does not allow identification of any individuals or individual communities.

Fieldworkers will administer the electronic questionnaire in a secluded spot in the homestead, taking care to maintain privacy throughout the interview. The questionnaires will not record names and no individual will be identifiable in the database derived from the questionnaires.

Digital records will be kept securely on the server in Botswana and will be accessible only to the principal investigators and to those they explicitly delegate to assist in data analysis. Original paper consent forms, will be securely transported, stored, retained and finally destroyed in accordance with CIET guidelines for security, storage and eventual destruction of paper records, available on our website (www.cietresearch.org).

#### Minimising potential risks to participants

The survey and finger-prick blood sample do not present more than minimal risk to participants. Finger prick blood sampling involves minor discomfort. We will train fieldworkers thoroughly in the procedure for obtaining finger prick blood samples and undertaking the rapid testing procedure, and assess their competence before allowing them to work in the field teams. The field workers will refer participants who test positive on the rapid HIV screening test to the local government clinic for confirmatory testing, counselling, and treatment if appropriate.

### Knowledge translation and exchange

The project takes a participatory approach to knowledge translation, involving research users throughout the research process [73]. Government partners, young women and service providers in the intervention districts have already contributed to the research design. Initial design workshops with government counterparts will finalise design and implementation. Management meetings during the project with government counterparts will update them on progress, share problems and seek solutions. Interim results dissemination meetings with local stakeholders will share preliminary findings, and discuss any required modifications to the process.

As results become available at the end of the trial, dissemination workshops will share findings with government and non-government stakeholders in Botswana. The research team will present findings at conferences in Africa and elsewhere, where possible involving research users in this process, and publish articles on the research process and findings in peer reviewed journals.

## Discussion

The presently funded project is the first stage of a longer national process implementing an HIV structural prevention package in waves of five districts in a stepped-wedge design. If funding is available, we will start the intervention package in the second wave of districts once the impact survey in the first and second wave districts is completed (in year 5). The second wave intervention package will include modifications based on the experience during the first wave of implementation. With the Government of Botswana, we will seek funding for extension of the intervention and impact measurement from national and international sources. If the first and/or second waves of interventions are successful in reducing HIV infections, the government may decide to roll out the package in all remaining districts as rapidly as possible.

### Potential achievements related to the research

This project illustrates a health development approach that may be of wider relevance. It identifies choice disability leading to disproportionate HIV risk. The resulting intervention opens a dialogue about the nature of the exclusion with the communities and the services in the context of the structural shifts in favour of young women. Even if the structural shifts (for example, young women entrepreneurs with purchasing power and self esteem to make transactional trans-generational sex less worthwhile) affect relatively few women, the logic for inclusion of young women shifts the meaning of the “presumed average citizen” as the target for services. This shift to include the most vulnerable, without taking away services from other beneficiaries, effectively strengthens systems, increasing coverage and, potentially, effectiveness and efficiency.

Gender violence, distorted traditionalist views of gender hierarchy, gendered economic dependence and alcohol abuse all lead to choice disability in HIV prevention. Enabling choices shifts power balances and reduces the worst effects of the disdain for the safety of others that is often part of sexual violence and transactional sex. Importantly, by increasing the number who can choose existing prevention actions – such as abstention, condom use or reduced concurrency -- purposive enabling of choice will release the potential impact of other HIV prevention strategies. INSTRUCT will help fill in the gaps in the literature and move the field forward by documenting the effect that a package of combined structural and behavioural interventions has on HIV infection among the age group that matters most for HIV prevention.

### Risks and mitigation strategies

The project includes re-targeting government structural support programmes towards those most vulnerable to HIV. This involves intensive cooperation from the government bodies responsible for implementing these programmes. Although these bodies at national level have expressed support for the project in principle, it may be hard to translate into a different way of doing business in practice. Among other changes, this will require increased support for the most vulnerable programme beneficiaries and increased monitoring of the programmes.

Currently access to government structural support programmes is patchy and not ideal, even in terms of poverty alleviation, let alone HIV prevention. During the project we will work with government to develop more effective monitoring of the government programmes: What is the age, sex of the beneficiaries? What are the outcomes of grants and loans? We will also undertake intervention research to examine the implementation and processes of the intervention package. The risk of incomplete or ineffective implementation of program changes in favour of young women is a key challenge of INSTRUCT, and will be monitored and addressed throughout the project.

## Abbreviations

BVV: Beyond Victims and Villains audio-drama
CRCT: Cluster randomised controlled trial
DC: District Commissioner
FCM: Fuzzy cognitive mapping
FW: Focused workshop
HEA: Health education assistant
NACA: National AIDS Coordinating Agency
RCT: Randomised controlled trial
